## Abstract

**Background:**

Chronic diseases are a substantial public health issue worldwide and affect an individual’s quality of life. Due to the alarming rise in type 2 diabetes, health care that was primarily focused on diagnosis and treatment of the disease is increasingly focused on prevention and self-care. Patients who adhere to a constant and strict treatment regimen (physical activity, diet, medication) and regularly monitor their health are more likely to maintain self-care and health, prevent the exacerbation of the disease, and avoid the complications of diabetes (retinopathy, diabetic feet, etc). In recent years, many innovative devices that have become increasingly present in inpatient health care, such as mobile apps, are available to help patients maintain consistency in monitoring their health status. Mobile apps make it easier for individuals to monitor their self-care and illness and follow instructions regarding disease control.

**Objective:**

This study aims to determine the impact of mobile app use on self-care in patients with type 2 diabetes. We will evaluate and test the usefulness of the *forDiabetes* app as a tool to improve the self-care of individuals with type 2 diabetes.

**Methods:**

We will perform a double-blind randomized controlled trial. The study will include individuals aged over 18 years diagnosed with or have regulated type 2 diabetes who are treated in family medicine practices. Additionally, the individuals included in the study should not have any acute complications due to the consequences of type 2 diabetes. They will use an Android or iOS mobile phone and a blood glucose meter during the investigation. With the help of simple randomization, individuals will be divided into the intervention and control groups. Individuals in the intervention group will use the *forDiabetes* mobile app to monitor their self-care for type 2 diabetes. Individuals in the control group will not receive a particular intervention. Data will be collected using the *Self-care of Diabetes Inventory* questionnaire and *Brief Illness Perception Questionnaire.* Blood sugar, blood pressure, glycated hemoglobin (HbA_1c_), and weight measurements will be monitored using calibrated instruments during the study by the nurses employed at the family medicine practice. Data will be collected at the beginning of the study and after a patient visits the family medicine practice.

**Results:**

In the first half of 2020, we have prepared a translation of the mobile app that will be used by the participants of the intervention group, as well as more detailed instructions for using the app. We have also prepared a translation of the questionnaires in Slovene. The research results will be published in 2023.

**Conclusions:**

This research contributes to greater visibility and usability of mobile apps for the self-care of patients with type 2 diabetes and raises awareness of the possible use of innovative methods.

**Trial Registration:**

Clinicaltrials.gov NCT04999189; https://clinicaltrials.gov/ct2/show/NCT04999189

**International Registered Report Identifier (IRRID):**

PRR1-10.2196/31652

## Introduction

### Background

Type 2 diabetes is a complex chronic disease [1,2] with an enormous global burden that has substantial implications for human health [3]. The consequences of the disease cause substantial economic and social responsibilities [4] and pose a growing public health problem [5,6]. Preventing and limiting the progression of the disease is an urgent task worldwide [7] and remains an important challenge for individuals and society [8]. The self-care of type 2 diabetes is key to containing the disease [9,10], reducing disease complications, and improving quality of life [11]. By supporting patients with type 2 diabetes in healthier self-care behaviors, we can influence the outcome of the disease [5]. The constant monitoring of diabetes and lifestyle factors can contribute to better health [12]. Many complications are the result of uncontrolled disease [13].

The current COVID-19 pandemic affects the direction of and interrupts health care, disrupting long-term conditions including type 2 diabetes [14,15]. The need of self-care for patients with type 2 diabetes is increasingly present [16]; therefore, mobile technology has become an essential tool for promoting self-care [17]. The optimal use of mobile technologies is necessary to achieve benefits and optimal cost efficiency [18]. A mobile app strengthens self-care and contributes to better information, health education, and self-confidence in dealing with the disease [19]. Knowledge of mobile apps has been identified as an essential factor enabling independent disease management and self-care [20]. The use of new technology is one way to bridge the gap between patient needs and providing health care [21]. A mobile health app for patients with type 2 diabetes affects their knowledge of the disease, improves blood glucose control [22], and positively affects self-care [23]. In the future, mobile apps will represent an essential part of the health care system, so research in this area is needed [24]. Mobile apps show potential for disseminating self-care education [4]; improving motivation [25], disease symptom management, and patient experience [26-28]; helping patients with strict treatment requirements [29] and the adoption of a healthy lifestyle [30]; and reducing care costs [31-33].

As a guide to the self-care of individuals with type 2 diabetes using the mobile app, we will use the Middle-Range Theory of Self-Care of Chronic Illness. Self-care is a general concept built from 3 key ideas: self-care maintenance, monitoring, and management. Maintaining self-sufficiency (or self-care maintenance) refers to an individual’s behaviors to improve well-being and maintain health and stability. Self-care monitoring refers to the process of observing oneself due to changes in signs and symptoms. Self-care management is defined as responding to signs and symptoms when they occur [34,35].

### Objectives and Hypotheses

Objective 1 is to assess the impact of using the mobile app on the assessment of patient self-care. Hypothesis 1 states that in the intervention group of patients with type 2 diabetes, the self-sufficiency assessment at the first control visit will increase compared to the control group that did not use the mobile app.

Objective 2 is to assess the impact of mobile app use on disease perception. Hypothesis 2 states that in the intervention group of patients with type 2 diabetes, perception at the first control visit will improve compared to the control group that did not use the mobile app.

Objective 3 is to assess the impact of mobile app use on blood sugar and HbA_1c_ levels. Hypothesis 3 states that in the intervention group of patients with type 2 diabetes, blood sugar and HbA_1c_ levels at the first control visit will decrease compared to the control group that did not use the mobile app.

Objective 4 is to assess the impact of using the mobile app on the patient’s body weight. Hypothesis 4 states that in the intervention group of patients with type 2 diabetes, the body weight at the first control visit will decrease compared to the control group that did not use the mobile app.

Objective 5 is to assess the impact of mobile app use on the patient’s blood pressure values. Hypothesis 5 states that in the intervention group of patients with type 2 diabetes, the blood pressure value at the first control visit will decrease compared to the control group that did not use the mobile app.

## Methods

### Randomized Controlled Trial Design

To determine the effectiveness of using the mobile app on the self-care of patients with diabetes, we will conduct a double-blind randomized controlled trial. The study will include people aged over 18 years diagnosed with type 2 diabetes who are treated in family medicine practices in Slovenia. It will also include patients who have already been given some form of treatment to manage the disease and do not have chronic complications due to the disease (retinopathy, diabetic foot, nephropathy, neuropathy, etc). We will ensure this by receiving information on the patient’s health status from the medical staff. The patients will use a mobile phone and a blood glucose meter during the research period. Individuals will use the *forDiabetes* [36] mobile app in the intervention group. *forDiabetes* [36] is an existing app designed for diabetes self-care and allows the tracking and monitoring of crucial diabetes data (physical activity; high-carbohydrate foods consumed; blood glucose, blood pressure, and HbA_1c_ levels; weight; medications; etc). Before selecting the mobile app, its quality was assessed by 2 nurses using the Mobile Application Rating Scale: user version [37]. The mobile app was rated as high quality and suitable for patients (mean 4.54, SD 0.33; on a scale out of 5) by the nurses. In accordance with the American Association of Diabetes Educators, we also assessed whether the mobile app includes self-care behaviors [38]. The mobile app contains behaviors from the awareness of the social determinants of health, integration of technology into self-care, and role of the diabetes care and education specialist.

In the control group, individuals will not use any diabetes technologies to guide the self-care of their disease, but they will be using a blood glucose meter. The control group patients will manage their disease as before and attend scheduled checkups.

Before the start of the study and at the follow-up visit to the family medicine practice after using the mobile app, we will perform assessments of self-care and disease perception using the *Self-care of Diabetes Inventory* (SCODI) [39] and *Brief Illness Perception Questionnaire* (Brief IPQ) [40] instruments, respectively. A nurse employed at the family medicine practice will also monitor blood sugar, blood pressure, and glycated hemoglobin (HbA_1c_) levels and body weight in the intervention and control groups with standardized, validated instruments. The nurse will use the standardized calibration devices according to the guidelines for each measurement. Data will be recorded at each inspection. We will also collect the data that the patients will enter daily into the mobile app (physical activity; high-carbohydrate foods consumed; blood glucose, blood pressure, and HbA_1c_ levels; weight; medication; etc) in real time.

The research will be carried out in family medicine practices where individuals with type 2 diabetes are treated throughout Slovenia. The study will cover at least one private and one public family medicine practice from each regional unit in Slovenia. We will use a simple randomized approach to select the family medicine practices for cooperation from a preprepared list of family medicine practices. Before conducting the research, we will obtain the necessary consent from all institutions where the study will take place to enter the family medicine practices. We will also get the required permits from the individuals involved. At the beginning of the randomized controlled trial, we will obtain the written or oral consent of the institutions to participate in the research and enter their environment. The institutions will be provided with all necessary information and the research purpose. In the introductory part of the research, the participants in the study will be informed about the purpose and goal of the study, ensuring the anonymity of the participants, the voluntary nature of participation, and the possibility of withdrawing from participation. The survey will run for 1 year. Figure 1 presents a graphical illustration of the research process.

**Figure 1 figure1:**
[figure not shown]
Protocol for conducting a randomized controlled trail. HbA_1c_: glycated hemoglobin.

### Mobile App Translation

The mobile app *forDiabetes* [36] includes the required self-care behaviors according to the American Association of Diabetes Educators [38] and is suitable for maintaining self-care in individuals with type 2 diabetes. Before starting the research, we have obtained written consent to use the mobile app. *forDiabetes* [36] is an existing app translated from English into Slovene before the research was conducted. The text was translated by 2 researchers who have the necessary knowledge in self-care and English. In the case of wording deviations, there was a discussion between the researchers to find a Slovene word as close as possible to the meaning of the English word and used as professional terminology in the Slovenian language.

### Randomization and Blinding

Through simple randomization, the participants will be divided into the intervention and control groups, thus providing all participants with the same opportunity to be selected into any group in the study [41]. The randomization process will be blinded, as this will avoid the possibility of choice bias [42,43]. Blinded group assignment will be enabled using a group assignment software, which will allow a general random selection of the individual groups. The researcher involved in the randomization process and the patients themselves will not know to which group the patients were assigned. The medical staff will be informed about the start of the research and use of the mobile app by the individuals in the intervention group. The only difference between the intervention and control groups will be the use of the *forDiabetes* [36] mobile app, which the intervention group will use from the beginning of the study until the first control visit. Both groups will receive instruction regarding type 2 diabetes and the related self-care.

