### Data Collection

The initial part of the questionnaire consists of questions about the patient’s demographic data and data on the patient’s support from the medical staff. The first part of the questionnaire will cover the assessment of self-care. Self-care in patients with type 2 diabetes will be assessed using the SCODI instrument [39]. The tool consists of 40 assumptions classified into 4 dimensions: self-care maintenance (12 assumptions), self-care implementation (8 assumptions), self-care monitoring (9 assumptions), and self-confidence (11 assumptions). The instrument is assessed using a Likert scale, where a higher score represents better self-care [39]. We will also use the Brief IPQ scale [40] to assess disease perception. The questionnaire rapidly assesses disease perception and measures the patients’ cognitive and emotional representations of their disease. The questionnaire contains 8 questions graded on a 10-point scale and 1 open-ended question. There are 5 questions that assess the cognitive perceptions of the disease: consequences (point 1), timeline (point 2), personal control (point 3), treatment control (point 4), and identity (point 5); 2 questions that assess emotional representation: care (point 6) and emotions (point 8); and 1 question that estimates the comprehensibility of the disease (point 7). The assessment of causal representation is based on an open response that requires the patients to indicate the 3 most important causal factors in their disease (point 9) [40]. The nurses employed at the family medicine practices will use standardized, calibrated devices according to the guidelines to measure blood sugar, blood pressure, and HbA_1c_ levels and body weight. Data will be recorded at each control check.

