### Inclusion Criteria

A randomized controlled trial will be conducted in family medicine practices where individuals with type 2 diabetes are treated throughout Slovenia. There are 10 regional units of the Health Insurance Institute of Slovenia, with 241 private and 656 public health institutions [53]. The research will cover 1 family medicine practice from each regional unit. According to the data from January to September 2018, there were 28,593 treatments of individuals in connection with type 2 diabetes conducted in family medicine practices [54]. This number was used to calculate the sample size, which was calculated using a sample size calculator (Raosoft) [55] that has been used in many similar health research studies [56-59]. We used a power analysis and entered the necessary data with a 95% error rate and 5% confidence level. The required minimum sample size is 380 participants. We will include individuals aged over 18 years with type 2 diabetes who have already been given treatment. Additionally, there should be no acute complications due to the consequences of type 2 diabetes in the individuals included in the study. They must use a mobile phone and a blood glucose meter during the research period.

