### Limitations

The main limitation is that we will only include patients with controlled and managed type 2 diabetes in the study, which means that we will examine only a specific part of the population. The study will also have only patients treated in family medicine practices, which may prevent the possibility of generalization to all people with type 2 diabetes. 

Having both control and intervention groups at the same family medicine practices may provide bias, as this will not conceal the allocation of an intervention in a randomized controlled trial. Researchers will know in which group the participants were assigned, as these participants will carry out the necessary training for the use of the mobile app and other interventions. The research will use a questionnaire to assess the participants’ self-care and perception of the disease, which can provide socially expected and desirable answers.

Our study contains the following assumptions. People with type 2 diabetes have deviations or shortcomings in each concept of self-care. The app will affect a patient’s self-care with type 2 diabetes and other critical clinical measures. Self-care and disease perception are measurable and that the translated questionnaire will be helpful in our research. Medical professionals, employees in family medicine practices, and individuals with type 2 diabetes will be willing to participate in the study. People with type 2 diabetes will actively use the mobile app and monitor their health through data entry. The results expected during the study are changes in self-care; disease perception; blood sugar, blood pressure, and HbA_1c_ levels; and measured body weight.

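### Simple randomisation and an unadjusted comparison both ignore practice; validity is not affected, but some precision is lost that could be kept cheaply

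*Protocol article*

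**What the plan says.** **Allocation.** Randomization and Blinding: "Through simple randomization, the participants will be divided into the intervention and control groups". Each patient is to have an equal chance of either arm, which implies a 1:1 ratio. Group assignment software is to be used. No stratification or blocking by practice is mentioned.

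**Both arms in each practice.** Limitations: "Having both control and intervention groups at the same family medicine practices may provide bias".

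**Who measures.** Data Collection: "The nurses employed at the family medicine practices will use standardized, calibrated devices according to the guidelines to measure blood sugar", as well as blood pressure, HbA1c and body weight.

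**Analysis.** Statistical Analysis names an independent-samples t test or a Mann-Whitney U test, chosen by the distribution of the variable, at a significance level of 0.05. It mentions no practice term.

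**Number of practices.** Randomized Controlled Trial Design: "The study will cover at least one private and one public family medicine practice from each regional unit in Slovenia". Inclusion Criteria: "The research will cover 1 family medicine practice from each regional unit", and "There are 10 regional units of the Health Insurance Institute of Slovenia". The first gives at least 20 practices, the second 10.

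**The concern.** Practice is a grouping factor known at entry, and there are several reasons why outcomes may differ between practices: the nurses who measure, case mix, support from staff, and the local timing of the first control visit, for which the article gives no interval. Simple randomisation across the whole trial leaves the split within each practice to chance. The unadjusted test then leaves between-practice variation in the error term.

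Precision is at stake. Some of the information bought with 380 patients would be lost for want of an allocation setting and a model term. The allocation method cannot be changed for patients already randomised, so this is best settled before enrolment.

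**Working it through.** **Inputs.** N = 380, 10 regional units, 1 or at least 2 practices per unit, and 1:1 simple randomisation (protocol article). Assumed: equal practice sizes, so 10 practices of 38 or 20 of 19; a share of outcome variance between practices (ICC) of 0.02 to 0.10.

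**1. The plan's own figure.** Read as 95% confidence and a 5% margin of error, with proportion 0.5 (assumed) and the stated population of 28,593, let x = 1.96² × 0.25 = 0.9604. Then n = 28,593 × 0.9604 / (28,592 × 0.0025 + 0.9604) = 379.08, rounded up to 380. The figure reproduces as a survey precision size. Practice plays no part in it.

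**2. Imbalance within practices (exact binomial, probability 0.5).**
- 20 practices of 19: 2 × P(X ≥ 13) = 0.167 per practice. Expected number 20 × 0.167 = 3.3.
- 10 practices of 38: 2 × P(X ≥ 24) = 0.143 per practice. Expected number 10 × 0.143 = 1.4.
- The two cut-offs differ (68% and 63% in the larger arm). At a common cut-off of 2:1 or worse, the chance per practice is 16.7% with 19 patients and 3.4% with 38.

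**3. Bias and test level.** In simulations of 8,000 trials per setting (10 or 20 practices, ICC 0.02, 0.05 and 0.10), the mean error of the unadjusted difference was at most 0.002 SD, which is zero within simulation error. The type I error of the t test was 4.7% to 5.3%.

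**4. Precision.** The variance of the unadjusted difference under simple randomisation is 4·SD²/N. With stratification by practice and a practice term it is 4·SD²·(1 − ICC)/N. The standard error ratio is therefore 1/√(1 − ICC), and the loss in patients is 380 × ICC. Power is for an assumed effect of 0.2875 SD with 190 per arm.

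| ICC | SE ratio | Patients lost | Power, plan | Power, stratified with practice term |
|---|---|---|---|---|
| 0.02 | 1.010 | 7.6 | 80.0% | 80.8% |
| 0.05 | 1.026 | 19 | 80.0% | 82.0% |
| 0.10 | 1.054 | 38 | 80.0% | 84.0% |

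The chance contribution of practice to the difference has SD 2·√(ICC/380), which is 0.015 to 0.032 outcome SDs, against a total standard error of 2/√380 = 0.103.

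**5. What a practice term alone recovers if simple randomisation stays.** Let P be the number of practices and m their size. A practice with a:b patients keeps 4ab/m² of the information of an even split, on average 1 − 1/m: 94.7% for m = 19 and 97.4% for m = 38.
- Fixed practice effects multiply the variance by (1 − ICC)/(1 − 1/m). They gain only if ICC exceeds 1/m, that is 0.053 for m = 19 or 0.026 for m = 38.
- A random practice effect also uses the between-practice information: I = P(m − 1)/[4(1 − ICC)] + (P − 1)/[4(1 − ICC + m·ICC)], in units of 1/SD². Compare this with 380/4 = 95 for the unadjusted test and 95/(1 − ICC) for the stratified design with a practice term. The share of the loss recovered is (I − 95)/(95/(1 − ICC) − 95).

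| ICC | Stratified | I, 10 × 38 | Recovered | I, 20 × 19 | Recovered |
|---|---|---|---|---|---|
| 0.02 | 96.94 | 95.68 | 35% | 95.33 | 17% |
| 0.05 | 100.00 | 98.16 | 63% | 97.24 | 45% |
| 0.10 | 105.56 | 103.26 | 78% | 101.70 | 63% |

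A practice term alone thus recovers most of the loss where the loss is largest, and less where it is small.

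**The case against.** The strongest reply is that simple randomisation of individuals is a valid, explicitly stated choice. Chance imbalance between practices is already counted in the ordinary standard error. Because past assignments say nothing about the next one, simple randomisation is also the least predictable scheme. That matters here: medical staff will know about app use in the intervention group, and Limitations concedes that allocation will not be concealed within a practice. Blocking within practices gives up some of this unpredictability for a small gain. A practice term might also appear in an analysis plan that is not shown. Most of this stands, and it limits the point to efficiency. It does not remove it: the article names an unadjusted test, and a practice term carries no predictability risk.

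Three stronger readings are tempting but not supported:

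- A reader might infer that practice differences bias the app effect. Allocation is by individual, so they enter only as chance error (step 3).
- A reader might infer that each practice's nurse also instructs the patients. The article says that both groups receive instruction but does not say from whom. It assigns only the measurements to practice nurses, with standardised, calibrated devices, which limits one source of difference. The self-care and illness perception outcomes come from questionnaires, so differences in nurse measurement do not bear on them.
- A reader might infer that uneven practices contribute little. A 13:6 split keeps 4 × 13 × 6/19² = 86% of the within-practice information, and 24:14 keeps 4 × 24 × 14/38² = 93%.

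**Conclusion.** The point holds as a modest, cheaply avoided loss of precision. Neither the stated allocation nor the stated test takes account of practice. The standard error is about 1% to 5% larger than with stratification and a practice term, equivalent to roughly 8 to 38 of 380 patients, and moderate imbalance in some practices is likely. Validity is not threatened. The size rests on an assumed ICC of 0.02 to 0.10 and equal practice sizes; the document gives neither. With unequal sizes, small practices would be more uneven. The case for acting rests on the low cost, and on the fact that allocation cannot be redone after enrolment.

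**What to change.** 1. Reconcile the number of practices between Randomized Controlled Trial Design (at least 20) and Inclusion Criteria (10). It sets the stratum size.
2. At minimum, in Statistical Analysis, replace the unadjusted comparison with a model that includes practice. If simple randomisation is kept, enter practice as a random effect, because with small practices fixed effects can cost more than they save (step 5). If a rank test is needed, use one stratified by practice, such as the van Elteren test.
3. Preferably also, in Randomization and Blinding, replace simple randomisation with centrally generated 1:1 randomisation stratified by practice, using permuted blocks of randomly varying size that are not disclosed to practices, with assignment after baseline assessment. Keep the practice term, since the precision gain needs both.

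**Cost.** No extra patients: one model term, one or two protocol sentences and an allocation setting. The article does not name the software, so check that it can stratify. The downside is that allocations become slightly more predictable to staff who know who uses the app. Central assignment after baseline and undisclosed, varying block sizes keep this small. If the team judges that risk too high, step 2 alone is a reasonable compromise.

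### The trial is labelled double-blind, but patients will know their arm because app use is the only difference and no sham is described

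*Protocol article*

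**What the plan says.** The label appears twice in the protocol article. The Abstract (Methods) says "We will perform a double-blind randomized controlled trial", and Randomized Controlled Trial Design says "we will conduct a double-blind randomized controlled trial".

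Randomization and Blinding explains it this way: "The researcher involved in the randomization process and the patients themselves will not know to which group the patients were assigned". The same section describes software-based assignment and says that app use is all that separates the arms. It also says "The medical staff will be informed about the start of the research and use of the mobile app", referring to use by the intervention group.

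On treatment, the Abstract says "Individuals in the intervention group will use the *forDiabetes* mobile app to monitor their self-care for type 2 diabetes" and "Individuals in the control group will not receive a particular intervention". The design section adds: "The control group patients will manage their disease as before and attend scheduled checkups". Controls use a glucose meter but no other diabetes technology. No sham or comparator app is described.

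The Limitations section says "Researchers will know in which group the participants were assigned". It also says that placing both groups in the same practices will leave the allocation unconcealed, and that the questionnaires may attract socially desirable answers.

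**The concern.** A double-blind label tells readers, ethics reviewers and meta-analysts that at least two parties, normally the patient and the investigator or assessor, do not know the arm. Here the patient must know, and the article's own Limitations section says that researchers will know.

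This matters most for Hypotheses 1 and 2, on self-care (SCODI) and illness perception (Brief IPQ). Both are completed by the patient, and self-care is the trial's stated aim. A patient who has been asked to use a self-care app may report better self-care because it is expected. If that tendency differs between arms it becomes part of the estimated effect, and randomisation does not remove it. Blood pressure and weight, taken by practice nurses, are also exposed if the nurse knows the arm, though less so.

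**Working it through.** **1. Who could be blinded, from the text.**

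| Party | What the article says | Can blinding hold? |
|---|---|---|
| Patients | Said not to know their group (Randomization and Blinding). Intervention patients use a named app with daily entry; controls continue usual management; app use is the only difference; no sham described | No, once the app is in use |
| Researcher doing the randomisation | Said not to know (Randomization and Blinding) | Possibly, at assignment |
| Researchers generally | Said to know, in connection with app training (Limitations) | No |
| Practice staff, including the measuring nurses | Informed of app use by the intervention group (Randomization and Blinding) | Not stated; awareness is the plain reading, but a patient list is not mentioned |

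The patient row alone defeats the label. The other rows show that no party is clearly described as blinded after assignment, with the possible exception of the randomising researcher.

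**2. Concealment is a separate question.** Randomization and Blinding describes a blinded, software-based assignment intended to avoid choice bias, which is the purpose of allocation concealment. Limitations says that allocation will not be concealed. The article therefore does not settle whether the next assignment is hidden from the person enrolling.

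**3. The article's own sample-size figure.** The 380 under Inclusion Criteria is the only sample-size figure. The finite-population survey formula is n = N·x / ((N − 1)·E² + x), with x = z²·p(1 − p). With N = 28,593, z = 1.96, E = 0.05 and p = 0.5 (p is not stated in the article), x = 0.9604 and n = 379.08, rounded up to 380. The figure reproduces. The blinding point does not depend on it; it serves only to set an arm size below.

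**4. Illustration of what differential reporting could do.** Inputs: an equal split of 380, so n = 190 per arm (assumed); a two-sided t test at 0.05 (Statistical Analysis names the t test as one option); no true effect; and a pure reporting shift of d SD in the app arm (assumed, as the article gives no figure).

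The noncentrality is d·√(n/2) = d·√95, with 378 degrees of freedom and a critical value of 1.966.

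| Assumed shift d | d·√95 | Probability of a significant result |
|---|---|---|
| 0 | 0 | 0.050 |
| 0.1 | 0.975 | 0.163 |
| 0.2 | 1.949 | 0.494 |
| 0.3 | 2.924 | 0.831 |

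Simple randomisation does not guarantee equal arms. With 380 patients the SD of one arm's size is √380/2 = 9.7, so a split of 171 to 209 lies about two SDs out. There the noncentrality is d·√(171·209/380) = d·√94.05, and the probabilities for shifts of 0.1 and 0.2 are 0.162 and 0.490. The equal-split assumption hardly matters; the assumed shift does.

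**The case against.** **The blinding paragraph may be about assignment.** It is mostly about how patients are allocated, and can be read as loosely worded concealment. That reading stands as an explanation of how the wording arose. It does not rescue the label, which is applied to the whole trial, or the sentence about patients.

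**The researcher statements need not conflict.** A reader might infer that Randomization and Blinding and Limitations flatly contradict each other on researchers. The first speaks of the researcher involved in randomisation, the second of researchers in general, and these may be different people. This objection stands: the two sections need reconciling, but a strict contradiction on that role is not shown.

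**Staff may not know individual allocations.** A reader might infer that staff are told which patients have the app. The text says that they are informed of app use by the intervention group, which could mean only that such a group exists. Patient-level knowledge is plausible, not stated. Standardised, calibrated devices are also specified for the measurements, a partial safeguard.

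**The problem is partly disclosed.** Limitations admits that researchers will know the groups, that allocation is not concealed and that answers may be socially desirable. So it would be too strong to say that the article hides the risk. But the disclosure sits beside a label that says the opposite, and the Abstract carries only the label.

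**The error rates do not measure the mislabelling.** Correct. They describe any unblinded questionnaire trial under assumed shifts and would be the same under an honest label. They show only what kind of bias the label wrongly implies is controlled.

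**Conclusion.** The double-blind label and the claim that patients will not know their group are wrong as written. This rests on the article's own description of the two arms and needs no assumption beyond the absence of a sham, which none of its sections mentions.

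The consequence falls mainly on SCODI and Brief IPQ, which will be unblinded self-report. The size of any resulting bias is unknown. The figures of about 16% and 49% are conditional on assumed shifts of 0.1 and 0.2 SD and on 190 per arm; they are not estimates for this trial.

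Three stronger readings should not be drawn. The documents do not state that the nurses receive individual allocations. They do not show that the randomising researcher is among those who will know. And controls are not untreated: they continue their usual management, use a glucose meter and, like the app arm, receive self-care instruction.

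**What to change.** 1. In the Abstract and in Randomized Controlled Trial Design, replace double-blind with open-label.
2. In Randomization and Blinding, delete the claim that patients do not know their group.
3. Reconcile Randomization and Blinding with Limitations: state whether the allocation is hidden up to the moment of assignment, by what procedure, and which researchers know it afterwards. Claim concealment only if that procedure delivers it; adding the phrase without doing so would replace one unsupported label with another.
4. State what practice staff are told. Where feasible, do not tell the nurse taking the follow-up measurements which patients have the app.
5. State that SCODI and Brief IPQ results come from unblinded self-report and are open to differential reporting.

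The cost is wording in three or four sections and one instruction to practices. The downside is a less favourable design label. Item 4 may not be achievable in practices where the same nurse supports the patients day to day; if so, the article should say that the assessors are not blinded.
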